**Fig. 1 Fig1:**
[figure not shown]
An overview of the study’s stepped wedge design

### Sample size calculation

The stepped wedge design used for this study is a variant of a Cluster Controlled Trial where all clusters receive the intervention in a randomised order. Taking into account the possibility of intra-cluster correlation [16], an effect sample size for physical activity observations was calculated using ESS = (m × k/DE) assuming that schools will have an average of 500 students enrolled, the design effect was 0.05. It was calculated that 1661 students would need to be observed to provide adequate power to detect a difference between clusters receiving the intervention.

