### Recruitment and study participation

The HAPPY Study will be conducted in six New South Wales Department of Education and Communities (NSWDEC) schools, in the Metropolitan Sydney Region (approx. 33.51°S, 151.12°E). All eligible schools will be sent an invitation to participate by the NSWDEC Schools Sport Unit. Schools that express an interest in participating will be contacted by the research team, and will be provided with more information about the study and intervention.

To participate, schools will be required to provide school level consent for the physical activity observational data collection from the principal, and all students participating in the behavioural, and the social support data collection will be required to provide parent/guardian consent. Teachers will not need to provide consent to participate in the intervention, as no information identifying them will be recorded or reported on.

All six schools will be participate in baseline data collection during the same school term and randomisation into stepped intervention groups will take place after the baseline data.

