### Statistical methods

Using the Statistical Package for Social Sciences (SPSS, v21), descriptive statistics and measures of central tendency will be used to describe the effect of the intervention from baseline to follow-up data in each step of the study.

Regression analysis will be completed for this study, to determine genuine relationships between the intervention, and the outcomes for physical activity levels, students’ on-task behaviour time, and frequency of social support for physical activity. Mixed-model ANCOVAs in SPSS will be computed, and each mixed model will be fitted to the data using the restricted maximum likelihood method. Percentage of occurrence (i.e. frequency) data will be analysed using ×2. For each mixed model, sex will be included as fixed effects, with the school included as a random effect to account for the effects of stepping by school. This is a standard statistical procedure for analysis of clustered datasets [27].

Intra-cluster comparisons will be completed between control and intervention periods, and for analyses involving school level characteristics of physical activity, the unit of analysis will be one scan of one area.

If schools decide to stop participating in the study, data pertaining to that school will not be included in the final analyses. Likewise, if a student selected for the behavioural observation component of the study decides to stop participating in the study their data will not be used in the final analyses. For all other components of the study (i.e., physical activity observation and Social Support), intention to treat principles will be followed and all possible data collected will be analysed.

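### The printed design effect of 0.05 is not a valid design effect for schools of 500, and 1661 does not follow from it, so the claim of adequate power is unsupported as written

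*Protocol article*

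**What the plan says.** All quantities below are from the protocol article, section Sample size calculation, unless noted.

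- The method: "an effect sample size for physical activity observations was calculated using ESS = (m × k/DE"), offered as allowing for correlation within schools.
- The inputs: "assuming that schools will have an average of 500 students enrolled, the design effect was 0.05".
- The result: "It was calculated that 1661 students would need to be observed to provide adequate power to detect a difference between clusters receiving the intervention".
- The number of clusters, from Recruitment and study participation: "The HAPPY Study will be conducted in six New South Wales Department of Education and Communities (NSWDEC) schools".

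The paragraph gives no ICC value, effect size, significance level or numerical power. Study Design describes a stepped wedge in which every school starts as control and the intervention is introduced in three steps over 12 months. The section on physical activity during recess and lunch plans 12 scans per school per term and 288 in total, which implies four terms (288 / (6 × 12) = 4). Statistical methods adds that, for analyses of school-level characteristics of physical activity, "the unit of analysis will be one scan of one area".

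**The concern.** A design effect is the factor by which clustering inflates the variance. When pupils in the same school resemble each other it exceeds 1, and for schools of 500 it can be large. A value of 0.05 says the opposite: that clustering makes each pupil worth twenty independent ones. That contradicts the purpose of a paragraph written to allow for clustering.

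This paragraph is the only justification of trial size in the article. If its one numerical input is wrong and its result cannot be traced to that input, readers cannot tell what difference the trial was sized to detect, or whether the calculation was meant for this design at all.

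**Working it through.** **1. The plan's own inputs.** With m = 500, k = 6 and DE = 0.05:

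- ESS = m × k / DE = 500 × 6 / 0.05 = 60,000, from 3,000 enrolled pupils.
- Working backwards, 1661 / 0.05 = 33,220 effective students, which corresponds to nothing in the article.

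So 1661 is not reproduced from the printed inputs.

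**2. Can DE be 0.05?** The usual form is DE = 1 + (m − 1) × ICC. Solving for the ICC at m = 500 gives (0.05 − 1) / 499 = −0.0019. Any ICC of zero or more gives DE of at least 1.

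**3. Reading 0.05 as the ICC (an assumption).**

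- DE = 1 + 499 × 0.05 = 25.95.
- 1661 / 25.95 = 64.01.
- A two-sample t-test at 0.5 SD, 80% power and two-sided 5% needs 63.8, so 64 per group.
- 64 × 25.95 = 1660.8, which rounds to 1661.

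The match is exact, but 0.5 SD, 80% and two-sided 5% are not in the article. Other inputs also give 64. As a two-group total it arises at 0.75 SD, one-sided, 90% power (32 per group), and for 10% versus 40% at 80% power (32 per group).

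**4. Does the formula describe the design?** ESS = m × k / DE contains a cluster size, a number of clusters and a design effect. It has no term for periods, steps, or the comparison of a school with itself before and after crossover.

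**5. What a stepped-wedge calculation would look like.** Assumptions: six schools, two per step (three equal steps), four terms with the first all control, and 1,661 observations spread evenly (1661 / 24 = 69.2 per school-term). Observations are taken as independent given school and school-term, total SD is 1, and critical values are normal. With cluster autocorrelation CAC:

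- between-school variance t = ICC × CAC
- variance of a school-term mean given the school, s = ICC × (1 − CAC) + (1 − ICC) / 69.2

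The Hussey-Hughes variance has I = 6, T = 4, U = 12, W = 56, V = 28. Then IU − W = 16 and U² + ITU − TW − IV = 144 + 288 − 224 − 168 = 40, so

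Var = 6s(s + 4t) / (16s + 40t).

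The difference detectable with 80% power is 2.80 × SE.

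| ICC | CAC | s | t | SE | Detectable difference | Power at 0.3 SD | Power at 0.5 SD |
|---|---|---|---|---|---|---|---|
| 0.05 | 1 | 0.0137 | 0.050 | 0.089 | 0.25 SD | 92% | over 99% |
| 0.05 | 0.5 | 0.0387 | 0.025 | 0.141 | 0.40 SD | 57% | 94% |
| 0.10 | 0.5 | 0.0630 | 0.050 | 0.182 | 0.51 SD | 38% | 79% |

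The detectable difference doubles across plausible correlations, so it has to be stated together with them.

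**The case against.** The strongest reply is that this is a labelling slip in a condensed article: the authors wrote design effect where they meant ICC, and the full protocol may hold the other inputs. Much of that stands. The slip is the likely explanation, and the absence of alpha, power and effect size from an article is not itself the complaint. But the printed value is wrong, and correcting the label does not turn the formula into a stepped-wedge calculation.

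Two stronger readings are tempting and are not supported.

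- **That the true requirement is double the stated one.** If 64 is a per-group figure, two groups need 128 × 25.95 = 3,322, more than the 3,000 pupils enrolled. This depends on an effect size, power and ICC that the article does not state, and other inputs make 64 a total. Enrolment is not a ceiling either. The calculation is for physical activity observations, and the 288 planned scans code every child present each time. Spread over them, 1,661 is about 5.8 codings per scan and 3,322 about 11.5.
- **That the trial is underpowered.** Treating 1,661 as the total of a parallel trial gives low power, but no parallel trial is being run. In the stepped-wedge illustration at ICC 0.05, power at 0.5 SD is about 94% to over 99%.

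Nor should the unit of analysis be overstated. The scan is the unit only for school-level physical activity analyses, so its mismatch with a count of students is partial.

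**Conclusion.** The concern holds in this form. The design effect of 0.05 is invalid for schools of 500 under any non-negative ICC, 1661 cannot be derived from the inputs given, and the formula shown ignores the stepped wedge. The claim of adequate power therefore has no support in the text.

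That 0.05 is the ICC, and that 1661 is 64 × 25.95 for one group of a parallel design, is the most natural reconstruction but remains an inference.

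The size of the problem is a missing justification, not a demonstrated shortfall. The illustrative detectable difference of 0.25 to 0.51 SD assumes that repeated codings are independent within a school-term. The same children may be coded in several scans and codings within one scan are likely to be alike, so these figures are probably optimistic and do not establish adequate power either.

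**What to change.** In Sample size calculation:

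1. If 0.05 is the ICC, say so, and give the design effect it implies (25.95 at m = 500). If it is something else, state what it is.
2. Withdraw 1661 as the number required.
3. Replace it with the detectable difference for the actual design (six schools, three steps, four terms, the planned scans per school-term) from a stepped-wedge variance formula, over a range of ICC and cluster autocorrelation. State the power and significance level used, and whether the count is of scans or of individual codings.

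Keep six schools; nothing here calls for more schools or pupils. The cost is one rewritten paragraph and a few hours of a statistician's time. The restated figure may also be less favourable than the present wording suggests.

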### Physical activity during recess and lunch

Observational data will be collected on student’s physical activity levels during lunch and recess breaks, and their utilisation of playground spaces for physical activity recorded using the System for Observing Play and Recreation in Communities (SOPARC) tool (CIAFEL, Portugal: http://activelivingresearch.org/soparc-system-observing-play-and-recreation-communities). This tool will collect student’s sex, their level of physical activity and environmental factors (i.e. time of day, temperature, recess/lunch break, presence of supervision).

SOPARC is a sampling technique in which systematic and periodic scans of individuals and environmental factors within predetermined target areas are made. Each school will have two predetermined target areas, identified by the Principal of participating schools as areas that students use frequently during recess and lunch. Following SOPARC protocols developed in a previous study [20, 21], trained researchers will complete two scans of each areas at both recess and lunch, three times during each term the study is running. The researchers are blind to the conditions of the intervention. Each school in the study will therefore be scanned 12 times each term, for a total of 288 scans across all schools during the study.

A scan involves panning from left to right, and coding each student in the area by sex (male or female), intensity of activity (Sedentary, Walking or Vigorous), and whether they are a Child, Teen, Adult or Senior. Additional data recorded for each scan will include; 1. Weather variables including temperature, rain and UV levels; 2. Time of day the observations were collected, and whether this was a lunch or recess period; 3. What type of activity the students are engaged in (i.e. handball, football, dancing, clapping games) and; 4. Teacher supervision and direction of physical activity. The SOPARC tool has been used by this research team to collect physical activity and sun-safe behaviours in primary schools, and was found to be efficient to use and had high degree of reliably, with an Intraclass Corelation Coefficient (ICC) of .912 [21].

Analysis of data collected with SOPARC will be done at an individual school level, between all schools during the same collection period and then completed on all data collected during the study.

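### The 1661-student target is in a unit that the playground scans do not record and the school-level analysis does not use, so it does not support the power claim

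*Protocol article*

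**What the plan says.** The Sample size calculation section states that "an effect sample size for physical activity observations was calculated". It works from school enrolment: "assuming that schools will have an average of 500 students enrolled, the design effect was 0.05". The result is that "1661 students would need to be observed to provide adequate power to detect a difference between clusters receiving the intervention". The figure is not divided by condition, step or term.

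The section Physical activity during recess and lunch describes how the data arise. "Each school will have two predetermined target areas", and a scan consists of "coding each student in the area by sex (male or female), intensity of activity (Sedentary, Walking or Vigorous") plus an age-group code. No identifier is listed. Observers make "two scans of each areas at both recess and lunch, three times during each term the study is running". The section then gives 12 scans per school per term and 288 in total.

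Under Recruitment and study participation, "The HAPPY Study will be conducted in six New South Wales Department of Education and Communities (NSWDEC) schools". These observations need consent at school level only. All schools share a baseline term, and randomisation to steps follows it.

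The Statistical methods section says that, for school-level characteristics of physical activity, "the unit of analysis will be one scan of one area". The mixed models with sex as a fixed effect and school as a random effect have no stated unit.

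**The concern.** The power statement is written in students. The instrument as described produces anonymous head counts of the same areas, rescanned within breaks, across breaks, across visits and across terms. A child who uses one of those areas regularly is coded many times, and nothing in the record links the codings. The one unit of analysis that the article states for physical activity is the scan. The target is therefore not the sample size of the data that will be collected and analysed.

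This matters because the article asserts adequate power on the strength of this number. In a stepped-wedge trial with six clusters, precision depends on the schools, the periods, the visits and scans within each school-period, and the correlations among them. Further codings of the same children add much less information than the same number of independent students. A reader who compared the final tally of codings with 1661 would learn nothing reliable about power.

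**Working it through.** **Inputs.** From the Sample size calculation section: the target of 1661, m = 500 enrolled per school, a stated design effect of 0.05, and the formula m × k / DE. From Recruitment and study participation: k = 6 schools. From Physical activity during recess and lunch: 12 scans per school-term and 288 in total. Not given anywhere: effect size, alpha, the power value, and children per scan.

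**Step 1: can 1661 be reproduced?**
- As printed: 500 × 6 / 0.05 = 60,000.
- Taking 0.05 as an intra-cluster correlation: DE = 1 + (500 − 1) × 0.05 = 25.95, and 3,000 / 25.95 = 115.6.
- Neither gives 1661.
- A reconstruction that comes close is 64 × 25.95 = 1,660.8. Here 64 is the per-group size of a two-sample t-test with a standardised difference of 0.5, two-sided alpha 0.05 and 80% power. The article states none of these three values, so this is a conjecture about the origin of the number.
- If the conjecture is right, the calculation treats each student as measured once, in clusters of 500. It contains no scans, terms or repeated measurement.

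**Step 2: scans available.**
- Stated schedule: 6 × 12 = 72 scans per term, and 288 / 72 = 4 terms.
- The schedule multiplied out: 2 areas × 2 scans × 2 breaks × 3 occasions = 24 per school-term, so 6 × 24 = 144 per term and 4 × 144 = 576 in all.
- The two counts must be reconciled. If 12 counts rounds that cover both areas, then 24 is the number in the unit of one scan of one area.

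**Step 3: children per scan at which codings reach 1661** (1661 / number of scans).

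| Scans per school-term | Whole study | Baseline term only |
|---|---|---|
| 12 (stated) | 1661 / 288 = 5.8 | 1661 / 72 = 23.1 |
| 24 (multiplied out) | 1661 / 576 = 2.9 | 1661 / 144 = 11.5 |

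**Step 4: range over an assumed head count, using the stated 12 scans.**

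| Children per scan (assumed) | Baseline codings (× 72) | Study codings (× 288) | Codings per enrolled pupil (/ 3,000) |
|---|---|---|---|
| 10 | 720 | 2,880 | 0.96 |
| 20 | 1,440 | 5,760 | 1.9 |
| 24 | 1,728 | 6,912 | 2.3 |
| 50 | 3,600 | 14,400 | 4.8 |

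Over the whole study, each of these head counts passes 1661. At baseline the total passes 1661 from 24 per scan and falls short at 20. Above 3,000 / 288 = 10.4 children per scan, codings outnumber the assumed enrolment, so some children must be counted more than once.

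**Step 5: the two readings.**
- *Distinct students.* The scans cannot show how many different children were seen, so the target cannot be checked against them.
- *Codings.* The target can be checked, but the codings are not independent and may fall in any mix of control and intervention periods.

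**The case against.** The strongest reply is that the same section speaks of physical activity observations, so students may be loose wording for student observations and the point only one of terminology. This stands in part: on that reading the number can be counted. It does not rescue the power claim, because repeated, unlinked codings that are not allocated to condition cannot be set against a requirement calculated from enrolled students.

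A second reply is that the scan unit is stated only for school-level characteristics. That is correct, and the sex-adjusted models may use individual codings. Those records would still be anonymous and repeated, so 1661 of them would still not be 1661 students.

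A third is that a condensed article may leave stepped-wedge power details to a full protocol or analysis plan. It may. The fault here is a power claim that the article does print, in a unit that does not fit the data.

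A reader might be tempted to go further in four ways that the article does not support:
- *The target both cannot be measured and is met at baseline.* These belong to different readings and cannot be asserted together.
- *It will be met before any school has the intervention.* This needs about 23 or more children per scan under the stated schedule. No head count is given, and 20 per scan yields only 1,440.
- *The plan sets no numbers in the relevant units.* It fixes six schools, 12 scans per school-term and 288 scans. What it lacks is a power claim expressed in them.
- *The team will claim power by re-counting children.* Nothing says that 1661 will be tracked, used as a stopping point or cited as achieved.

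**Conclusion.** The concern holds in a limited form. The article rests adequate power for physical activity on a number of students, while the data are unidentified repeated codings and the only stated analysis unit is the scan. The figure is therefore not the sample size of the planned data and does not support the claim.

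The unit mismatch follows from the text and needs no assumption. Its numerical size does depend on an assumed head count. With the stated 288 scans, about 5.8 children per scan brings the codings to 1661, so reaching that number would say little. Reaching it in the baseline term is possible but conditional.

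The point is separate from the implausible design effect, since a correctly inflated number of students would still be in the wrong unit. Both faults lie in the same calculation and are best corrected together. The collected data are not affected. What is at risk is the credibility of the power statement.

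**What to change.** In the Sample size calculation section, replace the 1661-student target with a statement for the schedule already fixed: six schools, the number of terms, visits per term and scans per school-term. Then give the power, or the detectable difference in a named scan-level outcome, under a stepped-wedge model with school clustering, with the assumed correlations and alpha.

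Make two related corrections in the same edit. First, replace the design effect of 0.05 with a correctly labelled quantity. Second, reconcile the 12 scans per school-term with the 24 that the schedule gives when multiplied out, since the new calculation needs one count.

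Call head counts student observations throughout, and do not treat reaching 1661 of them as evidence of power.

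The cost is some rewording and one calculation, with no extra schools, visits or scans. The resulting power statement may be less favourable than the present one.

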### Recruitment and study participation

The HAPPY Study will be conducted in six New South Wales Department of Education and Communities (NSWDEC) schools, in the Metropolitan Sydney Region (approx. 33.51°S, 151.12°E). All eligible schools will be sent an invitation to participate by the NSWDEC Schools Sport Unit. Schools that express an interest in participating will be contacted by the research team, and will be provided with more information about the study and intervention.

To participate, schools will be required to provide school level consent for the physical activity observational data collection from the principal, and all students participating in the behavioural, and the social support data collection will be required to provide parent/guardian consent. Teachers will not need to provide consent to participate in the intervention, as no information identifying them will be recorded or reported on.

All six schools will be participate in baseline data collection during the same school term and randomisation into stepped intervention groups will take place after the baseline data.

### Intervention design

The Peaceful Playgrounds Program is a primary school-based package that uses permanent playground markings, teacher training and accompanying resources to promote physical activity in playgrounds, teach fundamental movement skills, and support social skill development in students. The Peaceful Playgrounds Program will be used in the HAPPY Study as the intervention, and the effects of this on both physical activity levels, and behaviour in students measured.

Several research studies using either the Peaceful Playgrounds Program, or a similar playground based intervention, have shown changing playgrounds in primary schools to be more conducive to play, and supporting school teachers and students to make use of these spaces can significantly increase levels of physical activity, enjoyment of physical activity and improved social interaction skills (i.e. conflict resolution, and sharing) [17–19]. Peaceful Playgrounds will run a multi-component intervention that incorporates elements of environmental, and social intervention, as well as a teacher professional development to increase physical activity participation.

The environmental component of intervention involves the instillation of multi-coloured playground markings that act as visual prompts for students and teachers to be physically active. The markings will be designed specifically for each participating school, and teaching resources will be provided including games, activity suggestions and units of work that can be performed in relation to the markings. Accompanying equipment and play resources will be provided to schools to support engagement with the playground markings and increase physical activity.

Professional learning support will be offered to teachers at participating schools, which will include strategies for initiating play during breaks, games and activities that support the development of social skills in students such as sharing and self-regulation, and methods of supporting conflict resolution for the playground. The teacher training will also include an online network to provide a platform for teacher self-reflection, discussion forums and opportunities to interact with other participating teachers and the research team.

A Student Ambassador program will be implemented during the intervention to increase the social support students receive to be physically active. Selected students from Stage 3 (years 5 and 6) classes at each school will undertake a student leadership program to develop knowledge and skills to become physical activity ambassadors during break times. The students will be taught techniques from the Peaceful Playgrounds Program to initiate games and encourage social inclusion in their peers.

The Peaceful Playgrounds intervention is expected to increase vigorous physical activity levels in children, encourage participation and enjoyment of physical activity, and structure play in a way that supports socialisation and emotional well-being in children. The HAPPY Study will determine if Peaceful Playgrounds is an effective, efficacious, and scalable intervention.

